## Figures and Tables

**Table 1 healthcare-14-02416-t001:** Study variables.

Variable	Classification	Values	Source
Randomisation group	Dichotomous qualitative	Group A Group B	Ad hoc questionnaire
Sex	Polytomous qualitative	Female Male Prefer not to say	Ad hoc questionnaire
Age	Discrete quantitative	20–29 30–39 40–49 50–59 ≥60 years	Ad hoc questionnaire
Nationality	Nominal qualitative	Spanish Other	Ad hoc questionnaire
Educational level	Polytomous qualitative	Nursing Diploma Nursing Degree Master’s Doctorate	Ad hoc questionnaire
Sexual orientation	Polytomous qualitative	Heterosexual Homosexual Bisexual Asexual Other Prefer not to say	Ad hoc questionnaire
Primary care centre	Nominal qualitative	33 health centres in the MVGHD: Alameda–Perchel Alhaurín de la Torre Alhaurín el Grande Álora Alozaina Campanillas Capuchinos Carlinda Carranque Churriana Ciudad Jardín Coín Colonia Sta Inés-Teatinos Cruz de Humilladero Delicias El Cónsul El Palo Estación de Cártama Huelin La Luz La Roca Limonar Miraflores de los Ángeles Nueva Málaga Palma-Palmilla Portada Alta Puerta Blanca Puerto de la Torre Rincón de la Victoria San Andrés-Torcal Tiro Pichón Trinidad Jesús Cautivo Victoria	Ad hoc questionnaire
Type of employment	Nominal qualitative	Permanent Temporary Substitute	Ad hoc questionnaire
Years of experience in primary care	Ordinal qualitative	<1 year 1–5 5–10 >10 years	Ad hoc questionnaire
SABS Scale	Likert-type scale	Strongly disagree Disagree Neutral/Undecided Agree Strongly agree	SABS Instrument

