#### 3.1.1. Phase I: Quantitative Component (Pilot Cross-Sectional Survey)

Primary Outcome: To evaluate and compare self-reported attitudinal barriers and perceived comfort scores among primary healthcare nursing professionals when providing human sexuality counselling, as measured by the total and dimensional scores of the Sexuality Attitudes and Beliefs Survey (SABS).Secondary Outcome: To estimate the statistical relationship between these sexuality-related attitudes/beliefs and key sociodemographic and professional variables (specifically age, sex, years of experience in primary care, and previous training in sexual diversity).

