#### 4.2.5. Statistical Analysis

Statistical analysis will be conducted using open-source software Jamovi version 2.12.0 (The jamovi project, Sydney, Australia). The analytical process will be structured as follows:

Descriptive and exploratory analysis.

Categorical (nominal) variables are expressed as absolute and relative frequencies (percentages). For ordinal variables (Likert items) and non-normally distributed quantitative variables, non-parametric measures of central tendency and dispersion use median (Mdn), interquartile range (IQR), and minimum/maximum values.

Inferential analysis and hypothesis testing.

After verifying non-compliance with normality assumptions (Shapiro–Wilk test), non-parametric tests will be applied:Pearson Chi-square (χ^2^) for associations between categorical variables.Mann–Whitney U for two-group median comparisons.Kruskal–Wallis H for comparisons involving more than two groups.

Robustness and variability control.

Homogeneity of variances will be assessed using Levene’s test. Where heteroscedasticity is detected, appropriate robust adjustments will be applied. A 95% confidence level and statistical significance threshold of *p* < 0.05 will be set for all analyses.

Regarding the management of missing data, the mechanism of missingness will be evaluated using Little’s Missing Completely at Random (MCAR) test; if missing data exceed 5%, Multiple Imputation by Chained Equations (MICE) will be applied. To quantify the magnitude of the differences, appropriate non-parametric effect sizes will be calculated and reported: Rank-biserial correlation for Mann–Whitney U tests and epsilon-squared for Kruskal–Wallis tests. The internal consistency of the SABS instrument within our specific study sample will be rigorously assessed by calculating both Cronbach’s alpha and McDonald’s omega coefficients. Finally, to control the type I error rate during multiple comparisons, *p*-values will be adjusted using the Benjamini–Hochberg False-Discovery Rate (FDR) procedure where appropriate.

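### Experience bands overlap at 5 years, age bands are labelled quantitative, and the only listed test that fits either variable ignores band order and takes one variable at a time

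*Protocol article*

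**What the plan says.** Table 1 (Study variables) gives the response options for years in primary care as "<1 year 1–5 5–10 >10 years" and classes the variable as "Ordinal qualitative". It classes age as "Discrete quantitative", but the values listed are "20–29 30–39 40–49 50–59 ≥60 years".

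Section 3.1.1 sets the secondary outcome: "To estimate the statistical relationship between these sexuality-related attitudes/beliefs and key sociodemographic and professional variables". It names the variables: "specifically age, sex, years of experience in primary care, and previous training in sexual diversity".

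Section 4.2.5 lists three inferential tests: Pearson chi-square for categorical associations, Mann–Whitney U for two groups, and "Kruskal–Wallis H for comparisons involving more than two groups". The effect size for Kruskal–Wallis is epsilon-squared. No rank correlation, trend test or multivariable model is named.

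The Data Availability statement says that data collection has not yet started.

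**The concern.** There are two separate problems.

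**Recording.** The bands 1–5 and 5–10 share an endpoint, so two nurses with the same 5 years can tick different boxes. The label for age promises a number, while the form collects a category. An analyst cannot tell from Table 1 whether age is to be handled as quantitative or as ordered groups.

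**Analysis.** The aim is to estimate a relationship. Kruskal–Wallis asks only whether any band differs from the others. It makes no use of the order that Table 1 itself gives to experience, and epsilon-squared cannot show whether attitudes become more or less favourable with age. Because each variable is tested alone, an association that belongs to age can appear as an association with experience if the two are correlated. The discussion in the protocol article hopes that the findings will inform educational programmes, so the direction of an association, and the variable it belongs to, are the useful parts of this result.

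**Working it through.** **Inputs from the protocol article.** n = 112, 33 centres, average cluster size 3.4 and ICC 0.02 (section 4.2.2). Five age bands and four experience bands (Table 1). Threshold: "statistical significance threshold of *p* < 0.05 will be set for all analyses" (section 4.2.5), taken as two-sided.

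**The plan's own figure.** Deff = 1 + (m − 1) × ICC = 1 + 2.4 × 0.02 = 1.048, which reproduces the stated 1.05. Effective n = 112 / 1.048 ≈ 107. Clustering is ignored below; at this size it would lower every power slightly. The article states no power, effect size or SD, so the inputs in the next paragraph are assumptions.

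**Assumed.** A monotone relation with correlation ρ. Age bands holding 10/25/30/25/10% of nurses. Experience bands holding, for example, 10/25/25/40%. Age–experience correlation from 0 to 0.8.

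**Step 1: cost of ignoring order, by approximation.** Noncentrality λ = n ρ² / (1 − ρ²). At ρ = 0.25, λ = 112 × 0.0625 / 0.9375 = 7.47. Power comes from the noncentral chi-square, with 1 df for an ordered test, 3 df for Kruskal–Wallis on four bands and 4 df on five bands.

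| ρ | Ordered, 1 df | Experience, 3 df | Age, 4 df |
|---|---|---|---|
| 0.20 | 58% | 41% | 37% |
| 0.25 | 78% | 62% | 57% |
| 0.30 | 91% | 81% | 77% |

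The loss is about 10 to 17 points on experience and 15 to 21 points on age. These powers are somewhat optimistic because the same λ is used before and after banding.

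**Step 2: test and banding separated, by simulation (age, n = 112).**

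| ρ | Rank correlation, exact years | Rank correlation, bands | Kruskal–Wallis, bands |
|---|---|---|---|
| 0.20 | 53% | 50% | 29% |
| 0.25 | 73% | 70% | 47% |
| 0.30 | 87% | 85% | 64% |

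At ρ = 0.25, banding costs about 73 − 70 = 3 points and the choice of test about 70 − 47 = 23 points. The overlap at 5 years plays no part in these figures.

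**Step 3: misattribution.** The score depends on age only (correlation 0.25) and experience has no effect of its own. The table gives the share of studies with p < 0.05 for experience, and the power for age in the joint model.

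| Age–experience correlation | Kruskal–Wallis on experience alone | Experience in joint model | Power for age in joint model |
|---|---|---|---|
| 0 | 5% | 5% | about 75% |
| 0.5 | 13% | 5% | 64% |
| 0.7 | 25% | 5% | 48% |
| 0.8 | 29% | 5% | 36% |

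Repeats with other seeds and band proportions moved the second column by a few points. With a stronger age effect (0.3 SD per SD of age) it rises to 16%, 30% and 41% at correlations 0.5, 0.7 and 0.8.

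**The case against.** **The use of Kruskal–Wallis here is inferred.** Section 4.2.5 gives a general rule and mentions neither the secondary outcome, age nor experience by name. That is true. It remains the only listed test that fits a score compared across four or five bands, so this is the natural reading, but the article does not say it outright. Nor does it say whether scores are pooled across the two questionnaire versions for this outcome. A reader might infer pooling; the text neither pools nor stratifies.

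**Banding is not the culprit.** This stands. A reader might blame the bands for the whole power loss, or treat the experience variable as broadly misclassified because of the overlap. Banding age costs about 3 points, and the overlap touches only nurses at 5 years.

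**The joint regression does not buy back power.** This also stands. At an age–experience correlation of 0.7 its power for age is about 48%, practically the same as the 47% of Kruskal–Wallis. Its merit is the 5% error rate for experience.

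**Age and experience need not move together.** The variable is years in primary care, not years in nursing, and some nurses enter primary care late. A strong correlation is plausible but is not given in the article, and at zero correlation there is no misattribution.

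**Covariates and models are often left to an analysis plan.** This is fair as to the detail of a regression. It does not excuse response options that are printed with an overlap, or a named test that is a weak fit to the stated aim.

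**Conclusion.** The point holds in a limited form. The overlap at 5 years and the mislabelling of age can be read directly from Table 1. The listed test for more than two groups is a poor match for an aim of estimating relationships with ordered variables: it discards order and reports no direction.

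At n = 112 and a monotone correlation of 0.20 to 0.30, Kruskal–Wallis on age gives up roughly 21 to 23 power points against a rank correlation on the same bands. If only age matters, testing experience alone misattributes the effect in about 13% to 29% of studies over correlations of 0.5 to 0.8. All of these figures rest on the assumed effect sizes, correlations and band proportions, and the power loss requires a monotone relation, which the article does not assert.

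A reader might infer that real trends are bound to be missed, or that the study cannot tell which nurses need training. Neither follows. Section 4.2.2 configures Phase I as an exploratory pilot, this is its secondary outcome, and the comparison of Groups A and B is untouched. The correction is worthwhile because it is cheap now, and because exact years cannot be recovered once only bands are stored.

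**What to change.** Before the survey opens:

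1. Make the experience bands mutually exclusive in completed years (<1, 1–4, 5–9, ≥10), or ask for whole years.
2. Correct the classification of age in Table 1: ordinal if the bands stay, quantitative if age is asked in years. Keeping the age bands is acceptable, since they cost little power.
3. For age and experience, replace Kruskal–Wallis with an analysis that uses order (Spearman or a trend test), reporting direction and a 95% CI. Kruskal–Wallis can remain as description.
4. Add one regression of SABS total on age, sex, experience, training and questionnaire version, with centre as random intercept, reporting coefficients with 95% CIs. Previous training is named in section 3.1.1 but is missing from the variables in sections 4.2.3 and 4.2.4 and from Table 1, so a field for it is needed.
5. State that the regression is there to guard against crediting an age effect to experience, and that it is to be read beside the ordered one-variable results.

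**Cost.** A few survey fields and some wording. If exact age is collected it is slightly more identifying; restrict access and publish bands only. When age and experience are strongly correlated, the regression will give wide intervals.

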## Data Availability

Data sharing is not applicable to this article as no new datasets have been generated or analyzed yet. This manuscript describes a study protocol, and data collection will commence following the formal implementation of the described methodology.

## Abbreviations

LGBTQ+: Lesbian, Gay, Bisexual, Transgender, Queer. MVGHD: Málaga-Valle del Guadalhorce Health District. WHO: World Health Organization. SABS: Sexuality Attitudes and Beliefs Survey.
